**Figure 2 F2:**
[figure not shown]
The adjusted formula for sample size calculation. n = sample size, α = probability of type I error, β = probability of type II error, k = the ratio of 2 groups’ sample sizes, p = joint probability, p_e_ = incomplete circumferential resection margin rate of the experiment group, p_c_ = incomplete circumferential resection margin rate of the control group.

### Randomization and blinding

2.6

Due to the specificity and ethics, it is unlikely that any surgical center around the world would randomize patients to receive either L-ISR or L-ELAPE due to a lack of equipoise regarding the requirement for each operation in any particular patient. Direct comparison by a randomized controlled trial of the 2 procedures is currently virtually impossible. This trial allows the surgeons and outcome assessors to be aware of the whole assignment and all eligible patients will be informed of the treatment in detail on admission to hospital. However, statisticians responsible for the final analyses will be blinded.

### Data collection, management, and statistical analyses

2.7

For purpose of acquiring high-quality monitoring, we plan to employ several professional clinical investigators to collect and manage the data of all participants during entire trial performing. A Case Report Form (CRF) is designed for each participant to document their data. And we will upload the data of all participants to Research Manager (ResMan), an Electronic Data Capture (EDC) system, and the individual patient data (IPD) will be publicly accessed via Chinese Clinical Trial Registry (ChiCTR.org) within 3 years after completion of this trial.

SPSS for Windows, version 22.0 (IBM Corp, Armonk, NY) will be used for statistical analysis. The data are presented as the mean value **±** standard deviation for continuous variables and as a number for categorical variables. The difference of categorical data and continuous data will be compared with Student *t* test and chi-square test between the 2 groups, respectively. The Kaplan–Meier estimate will be used to analyze survival and fit survival curves. The multiple factor analysis will be performed by using Cox regression model.

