### Sample size

2.5

This is a non-inferiority verification study with QoL and efficacy as the main index. In the pilot study, incomplete CRM rate was 6.1% (2 out of 33 patients) in the L-ELAPE group. Based on the previous studies, we assume that the rate of incomplete CRM in the L-ISR group was 8.1% which was the average value in the meta-analysis.^[30]^ The adjusted formula below is used to calculate the sample size^[31]^ (Fig. 2). The “Pe” and “Pc” are the rates of incomplete CRM of the experiment group and the control group, respectively. The “k” represents the ratio of 2 groups’ sample sizes which equals 1 in this trial and “p” represents the joint probability. Setting type I error probability **α** = 0.025, type II error probability **β** = 0.2, the sample size required for each group is 72 cases. Furthermore, we assume that there will be a 20% dropout rate. Therefore, at least 159 patients are needed in this specific trial.

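### The trial is declared non-inferiority, but section 2.7 states only comparisons without a non-inferiority criterion; separately, it transposes the t test and the chi-square test

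*Protocol article*

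**What the plan says.** Section 2.5 (Sample size) of the protocol article fixes the hypothesis: "This is a non-inferiority verification study with QoL and efficacy as the main index". The calculation rests on incomplete CRM, which section 2.4 lists as a secondary outcome. In the pilot data the "incomplete CRM rate was 6.1% (2 out of 33 patients) in the L-ELAPE group", and 8.1% is assumed for L-ISR. With a type I error of 0.025 (sidedness not stated), a type II error of 0.2 and equal groups, the result is 72 per group. The readable text gives no non-inferiority margin. The legend to Figure 2 defines n, α, β, k, p and the two rates, but no margin symbol; the formula itself is not visible in the text at hand.

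Section 2.7 states the analysis. Data are summarised as mean and "standard deviation for continuous variables and as a number for categorical variables". The between-group comparison follows: "The difference of categorical data and continuous data will be compared with Student *t* test and chi-square test between the 2 groups, respectively". For survival, "The Kaplan–Meier estimate will be used to analyze survival and fit survival curves" and "The multiple factor analysis will be performed by using Cox regression model". No confidence limit, margin or non-inferiority test is mentioned for QoL or for incomplete CRM.

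**The concern.** There are two separate problems.

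First, the stated comparison does not address the stated hypothesis. A chi-square or t test takes zero difference as its null. Failing to reject that null shows only that the data are compatible with no difference; it does not exclude an important disadvantage, and failure becomes more likely as the sample shrinks. Non-inferiority requires the opposite null, that L-ISR is worse by at least the margin, to be rejected. At stake is the main oncological conclusion: whether sparing the sphincter costs an unacceptable number of involved resection margins.

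Second, *respectively* ties categorical data to the t test and continuous data to chi-square. Taken literally, the questionnaire scores, which are the primary outcomes in section 2.4, would be analysed by chi-square, and incomplete CRM, a yes/no outcome, by a t test.

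**Working it through.** **Inputs.** From section 2.5: pc = 0.061 (L-ELAPE), pe = 0.081 (L-ISR), α = 0.025 (taken as one-sided), power 0.80, n = 72 per group. Assumed for illustration, not in the document: true L-ISR rates of 16.1% (10 points worse) and 20.1% (14 points worse).

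**Step 1: which kind of test does 72 per group belong to?**

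Sum of variances: 0.061 × 0.939 + 0.081 × 0.919 = 0.05728 + 0.07444 = 0.13172.

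Multiplier: (1.960 + 0.842)² = 7.849. Product: 7.849 × 0.13172 = 1.0338.

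- As a test of difference: n = 1.0338 / 0.02² ≈ 2,585 per group. At 72 per group the exact power of the two-sided 0.05 chi-square test is only 7.7%.
- As a non-inferiority test with margin M: n = 1.0338 / (M − 0.02)². Setting n = 72 gives M − 0.02 = √(1.0338 / 72) = 0.120, so M ≈ 0.14. Check: 1.0338 / 0.12² = 71.8, rounded up to 72.

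The stated 72 is therefore reproduced only by a margin-based formula with a denominator of about 0.12². Three assumptions lead there: a 14-point margin with the 2-point disadvantage handled correctly; a 12-point margin that ignores the disadvantage; or a 10-point margin with the 2 points added in the wrong direction (with the correct sign, 10 points needs 1.0338 / 0.08² ≈ 162 per group). The text does not say which was used.

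**Step 2: how often would the stated chi-square test be non-significant when L-ISR is truly worse?**

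Exact enumeration: sum Bin(a; 72, 0.061) × Bin(b; 72, pe) over all pairs (a, b) for which the uncorrected two-sided chi-square p value is 0.05 or more.

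| True rates (L-ISR vs L-ELAPE) | Excess | Significant | Non-significant |
|---|---|---|---|
| 8.1% vs 6.1% (planning values) | 2 points | 7.7% | 92.3% |
| 16.1% vs 6.1% (assumed) | 10 points | 49.2% | about 51% |
| 20.1% vs 6.1% (assumed) | 14 points | 72.7% | about 27% |

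The last row sits on the margin that 72 per group implies when the sign is handled correctly. There, a one-sided 0.025 non-inferiority test should claim non-inferiority about 2.5% of the time. Taking non-significance as the criterion would do so about 27% of the time.

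**Step 3: one concrete result.** Suppose 9/72 with L-ISR and 4/72 with L-ELAPE. The difference is 12.5% − 5.6% = 6.9 points, and chi-square gives p = 0.15. The standard error is √(0.125 × 0.875/72 + 0.0556 × 0.9444/72) = 0.0474, so the Wald 95% interval is 6.9 ± 9.3, from −2.3 to +16.2 points; the Newcombe upper limit is 17.1. The difference is non-significant, yet the data do not exclude an excess of 14 points.

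**Step 4: the transposed tests.** No arithmetic applies. In section 2.7 the summary sentence treats the data types correctly (mean and SD for continuous, counts for categorical). The next sentence lists categorical then continuous, and t test then chi-square. Read in order, both pairings are reversed.

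**The case against.** Section 2.7 is a few sentences in a journal article. A full protocol or SAP may exist, and a confidence-interval decision rule is commonly placed there. A t test or chi-square procedure does not prevent an interval from being reported, and the unseen formula in Figure 2 may contain a margin. All of this stands, and it limits the claim. It does not remove the mismatch, because the article names its comparisons and none fits the hypothesis declared in section 2.5.

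Three stronger readings are tempting, and the document does not support them:

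- A reader might infer that p > 0.05 will be reported as non-inferiority. The article nowhere says so; what can be shown is that it states no other criterion.
- A reader might infer that the reversed tests are what defeats the non-inferiority claim, or that the primary scores will really be analysed by chi-square. The preceding sentence points to a word-order slip. Correcting the order would leave the missing criterion untouched.
- A reader might infer that tests of difference are the whole analysis. Kaplan–Meier and Cox are also planned, though without a non-inferiority criterion.

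It is also fair to say that the 16.1% and 20.1% rates are scenarios, that they concern a secondary outcome, and that no corresponding figure can be given for QoL. Finally, patients choose their operation, so an unadjusted interval set against a margin would still be open to confounding. That is a separate matter, which the change below does not settle.

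**Conclusion.** The point holds in this form: the hypothesis in section 2.5 is non-inferiority, the sample size fits only a margin-based calculation (72 per group, against about 2,585 for a test of difference), and the comparisons stated in section 2.7 carry no non-inferiority criterion. Non-significance cannot take its place, given non-significance rates of about 51% and 27% under assumed true excesses of 10 and 14 points. These figures assume 72 evaluable patients in each group, a 6.1% control rate and an uncorrected two-sided 0.05 chi-square test. The implied 14-point margin further assumes a one-sided 0.025 level and the correct sign for the 2-point disadvantage.

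The transposition is a separate editorial error, wrong as written and probably unintended. The mismatch between hypothesis and analysis should be corrected before the data are analysed, because the main conclusion depends on it.

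**What to change.** Revise section 2.7, with one addition to section 2.5:

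1. Correct the pairing: t test or linear model for continuous scores; chi-square or Fisher's exact test for categorical data.
2. For incomplete CRM, report the risk difference (L-ISR minus L-ELAPE) with a two-sided 95% confidence interval by Newcombe or Farrington–Manning; at 6.1% to 8.1% of 72, only about 4 to 6 events per group are expected. Claim non-inferiority only if the upper limit lies below the margin used in the sample-size formula. Write that margin and its justification into section 2.5. If it is not about 14 points, explain how 72 was obtained.
3. For QoL, report the mean difference with a 95% confidence interval. Either compare it with a pre-stated margin, or drop the non-inferiority claim for QoL.
4. State that a non-significant difference will not be read as non-inferiority.

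The cost is a few sentences and no new data. The real work is in stating and justifying the margin for incomplete CRM and, if the claim is kept, for QoL.

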#### Follow-up and dropping out

2.3.2

All participants will be followed up regularly as per schedule (Table 1) every 3 months for the first 3 years after surgeries. If necessary, biopsy and MRI will be performed to assess local or distant recurrence.

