**Table 1 T1:**
[figure not shown]
The schedule of follow-up after surgery.

Despite of written informed consent, patients are aware that they are free to discontinue their participation any time after it begins if:

1)the participant is not willing to continue on his or her own for any reason;2)adverse events which cannot be tolerated occur;3)the investigators remove a participant off for his or her good;4)the participant acquired some other treatment privately which will disturb the observation of this trial;5)pregnance happens to the participant during this trial, or6)the participant's adherence is poor.

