### Outcome measures

2.4

The primary outcomes of this trial are to be scores of European Organization for Research and Treatment of Cancer QoL questionnaire-core 30 (QLQ-C30), QoL questionnaire-colorectum 29 (QLQ-CR29), Wexner Incontinence Score, International Prostate Symptom Score (for male), International Index of Erectile Function-5 (for male) and Female Sexual Function Index (for female). General QoL is assessed basically by scores of European Organization for Research and Treatment of Cancer QLQ-C30 version 3.0^[24]^ and QLQ-CR29.^[25]^ Defecation functions (daily defecation, frequency, urgency, incontinence, differentiation between defecation and gas emission, pad use, antidiarrheal drug use, and the presence or absence of erosion around the anus) are evaluated by the Wexner Incontinence Score.^[26]^ Sexual function for men and women is assessed by using the International Index of Erectile Function-5^[27]^ and Female Sexual Function Index,^[28]^ respectively. Urinary function is assessed by using the International Prostate Symptom Score^[29]^ for men and color ultrasonography of residual urine volume for all.

The secondary outcomes include incomplete CRM rate, 3-year local recurrence, 3-year disease-free survival, 3-year overall survival, and other surgical outcomes. Incomplete CRM is defined as tumor within 1 mm from closest mesorectal fascia, or within 1 mm from closest levator muscle, or invasion into or beyond the insphincteric plane. Local recurrence is defined as recurrent disease in the pelvis or at the incision. Disease-free survival is defined as the time of surgery to recurrence or end of follow-up. Overall survival is defined as the time of surgery to the date of death from any cause or the end of follow-up. Surgical outcomes include operation time, intraoperative blood loss, temporary stoma, intraoperative perforation, time to first flatus, time to liquid diet intake, postoperative hospitalization days, postoperative complications, incidence of urinary retention, and postoperative mortality in 30 days.

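### The only method evident for the primary questionnaire scores is a two-sample t test, which can bias a late contrast if loss differs between L-ISR and L-ELAPE

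*Protocol article*

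**What the plan says.** Section 2.4 (Outcome measures): "The primary outcomes of this trial are to be scores of European Organization for Research and Treatment of Cancer QoL questionnaire-core 30", followed by QLQ-CR29, the Wexner score, IPSS and IIEF-5 for men, and FSFI for women.

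Section 2.3.2 (Follow-up and dropping out): "All participants will be followed up regularly as per schedule (Table 1) every 3 months for the first 3 years after surgeries". The reasons for leaving listed there include the patient's own wish, removal by the investigators, other treatment obtained privately, poor adherence, and that "adverse events which cannot be tolerated occur".

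Section 2.5 (Sample size): "Furthermore, we assume that there will be a 20% dropout rate".

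Section 2.7 (Data collection, management, and statistical analyses): "The difference of categorical data and continuous data will be compared with Student" begins the sentence on group comparisons. As printed, it gives the t test to categorical data and chi-square to continuous data; the reverse is evidently meant. The other methods named are Kaplan-Meier for survival and "The multiple factor analysis will be performed by using Cox regression model". Neither applies to questionnaire scores.

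**The concern.** A two-sample t test at one visit compares the patients who have a score at that visit. It makes no use of the scores that absent patients gave earlier. That is harmless if absence is unrelated to quality of life, or related to it in the same way and to the same extent in both groups.

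Nothing in the article supports either condition. Several listed reasons for leaving could be linked to how the patient feels. The Discussion describes different burdens: perineal wound problems and a permanent stoma after L-ELAPE; leakage, stricture and continence problems after L-ISR. Treatment is chosen by the patient and is not blinded. Death also ends the scores.

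The group that loses more of its patients with poor scores would look better than it is. Section 2.5 calls the trial a non-inferiority study with QoL as a main index, so a shift in either direction could create or hide a difference. This is separate from baseline confounding and would arise even between groups that were alike at the start.

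**Working it through.** **1. The plan's own dropout figure.** Section 2.5 needs 72 per group, 2 × 72 = 144, and states 20% dropout and a total of 159. With 20% the total would be 144/0.8 = 180, or 144 × 1.2 = 172.8, so 173. The 159 fits about 10% (144 × 1.1 = 158.4; 144/0.9 = 160) and is not reproduced. That is a separate matter. Here it means that 20% loss from 159 leaves 159 × 0.8 = 127.2 patients, about 63 per group.

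**2. Bias of a completers' contrast.** Let d be the proportion lost in a group and G the mean gap, in SD, between patients observed and patients missing. The full mean is (1 − d) × observed mean + d × missing mean, so the observed mean exceeds the full mean by d × G. The contrast is biased by d1·G1 − d2·G2. The article gives neither d by group nor G; all values below are assumptions that average 20% loss.

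| Loss, group 1 / group 2 | Gap (SD) | Bias (SD) |
|---|---|---|
| 20% / 20% | 0.5 to 0.8 in both | 0 |
| 25% / 15% | 0.5 to 0.8 in both | 0.05 to 0.08 |
| 30% / 10% | 0.5 to 0.8 in both | 0.10 to 0.16 |
| 20% / 20% | 0.5 to 0.8 in one group, 0 in the other | 0.10 to 0.16 |

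Example: 0.30 × 0.8 − 0.10 × 0.8 = 0.16. With SD 20, 0.05 to 0.16 SD is 1.0 to 3.2 points. Stacking both asymmetries goes further (0.30 × 0.8 − 0.10 × 0 = 0.24 SD), but is a more extreme assumption.

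**3. Effect on the error rate.** With 63 per group the standard error is √(2/63) = 0.178 SD. The two-sided 5% error for a bias b is 1 − Φ(1.96 − b/0.178) + Φ(−1.96 − b/0.178). It is 5.9% at b = 0.05, 8.7% at 0.10 and 14.6% at 0.16.

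**4. Simulation, assumed inputs.** 80 per group, 0-100 scale, SD 20, within-patient correlation about 0.6, five visits, no true difference. Loss depends on the last observed score unless stated. Biases are absolute, in points; Monte Carlo error is about 0.1 to 0.2.

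| Loss by group | t test on completers | Likelihood, all visits |
|---|---|---|
| 23% / 23%, same mechanism | 0.1 | 0.1 |
| 16% / 25% | 1.1 | not run |
| 11% / 29%, weaker dependence | 1.3 | 0.2 |
| 16% / 17%, informative in one group only | 2.1 | 0.0 |
| 15% / 34% | 2.3 | 0.0 |
| 12% / 33% | 2.9 | 0.2 |
| 12% / 33%, loss depends on the current, unseen score | 3.0 | 1.35 |

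The t test rejected in 8.9% of trials in the 15% / 34% case and in 10.2% in the 16% / 17% case. The latter shows that dropout rates need not differ; different reasons for leaving suffice. The last row shows the limit of the model.

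**The case against.** The strongest reply is that the article is silent on missing data, and a condensed article may leave missing-data handling and the analysis set to an analysis plan that is not shown. That stands as far as it goes: a reader might infer that the plan restricts the analysis to responders, and it does not say so. A t test could also be run on change scores or imputed data. But the point does not rest on silence. Section 2.7 names its methods, and a model for repeated scores would replace the one stated, not fill it in.

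Further objections hold in part:
- Questionnaire timing cannot be seen, because Table 1 is not shown. A reader might infer that the scores run to 36 months; the text fixes only participant follow-up at that length. The risk applies to any late visit.
- Recurrence is not among the listed reasons for leaving, and nothing says that forms stop at recurrence.
- The 20% is an allowance on a sample size for incomplete CRM, not a stated rate of missing questionnaires.
- The largest simulated biases come from strongly unequal loss (12% against 33%). At 16% against 25% the bias is about 1.1 points.
- The model's near-zero bias follows from simulating loss that depends on observed scores. When loss depends on the unseen score, the model's bias is 1.35 against 3.0 points: less than half, but not gone.

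**Conclusion.** The point holds in conditional form. The stated method for the primary scores can bias a late QoL contrast if the amount of loss or the reasons for it differ between the two operations. Under the assumptions shown, the size is roughly 0.05 to 0.16 SD, about 1 to 3 points on a 0-100 scale with SD 20. It is zero if loss is alike in both groups. The documents fix neither the size nor the direction.

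A reader might infer that the contrast will be biased. The documents do not support that: they give no loss by group and no difference between patients lost and retained, and equal informative loss cancels. What they do support is that the stated method offers no protection against a plausible problem, when a less biased analysis of the same data is available.

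**What to change.** In section 2.7, first put the two tests against the right data types. Then, for scores collected at more than one visit, replace the t test by a likelihood-based mixed model for repeated measures:
- use all available scores, with terms for group, visit and group-by-visit, and the pre-operative score if it is collected (the visible text does not say);
- use an unstructured within-patient covariance, or a simpler structure if there are too many visits for it. Scores at all 12 three-monthly visits plus baseline would mean 13 × 14/2 = 91 covariance parameters;
- report the group contrast at the chosen visit with its confidence interval;
- show questionnaire completion and deaths by group and visit;
- add one sensitivity analysis that shifts missing scores downward in each group.

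The cost is analysis wording; SPSS 22 fits the model, and no further patients or visits are needed. The downsides should be stated too. The model removes bias only from loss explained by observed scores; it reduces the rest without removing it. Scores after death are handled implicitly, so deaths must stand beside the QoL result. The change does not address confounding from patient choice of operation.

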### Study design

2.1

The study protocol follows the standard protocol items: recommendation for interventional trials (SPIRIT) guidelines.^[20]^ This is a prospective, single-central, non-randomized, non-blinded, phase I/II clinical controlled trial. All eligible patients will be assigned into 2 comparison groups (the L-ISR group and the L-ELAPE group) according to their own will after detailed preoperative conversations. The flow diagram of this trial is shown in Figure 1. Our trial started from September 2018 in West China Hospital of Sichuan University and is expected to end in 2021.

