#### Interventions

2.3.1

After assignment, patients in the L-ISR group will undergo standard L-ISR surgeries, while patients in the L-ELAPE group will undergo standard L-ELAPE surgeries with no intraoperative position change. Prophylactic ileostomy will be performed for selected patients with higher risk of anastomotic leakage in the L-ISR group. The radical laparoscopic-assisted surgery with meticulous total mesorectal excision and pelvic automatic nerve preservation (PANP)^[21–23]^ will be performed independently by 2 experienced and highly-specialized surgeons from the Department of Gastrointestinal Surgery, West China Hospital. Adjuvant chemotherapy, consistent with the preoperative neoadjuvant chemotherapy strategy for every participant, will continue within 4 to 6 weeks following surgery till completing 8 cycles. Closure of the ileostomy will be performed within 3 to 6 months after L-ISR according to rigorous preoperative assessment by digital rectal examination, colonoscopy, and barium enema examination.

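### The named Student t test can miss its 5% level if patient choice yields groups that differ in both size and spread; naming the Welch test is a free, minor safeguard

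*Protocol article*

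**What the plan says.** Section 2.7 names the tests in one sentence: differences in categorical and in continuous data, listed in that order, "will be compared with Student *t* test and chi-square test between the 2 groups, respectively". It mentions no variance assumption and no alternative test. Read literally, the sentence gives the t test to categorical data and the chi-square test to continuous data. The order is evidently reversed, and the t test is meant for the continuous outcomes.

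That covers the primary outcomes, because section 2.4 defines all of them as questionnaire scores: "The primary outcomes of this trial are to be scores of European Organization for Research and Treatment of Cancer QoL questionnaire-core 30 (QLQ-C30", followed by QLQ-CR29, Wexner, IPSS and IIEF-5 (men) and FSFI (women).

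On group sizes, section 2.1 assigns patients "according to their own will after detailed preoperative conversations". Section 2.5 takes the ratio of the two groups' "sample sizes which equals 1 in this trial" and arrives at 72 per group. No cap or quota holds recruitment to that ratio.

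On spread, section 2.7 says only how it will be reported: "The data are presented as the mean value ± standard deviation for continuous variables". No SD is given for any score in either group.

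**The concern.** The Student t test estimates one common variance from both groups. When the groups are of equal size, unequal variances hardly affect its error rate. When the variances are equal, unequal sizes do not affect it. It fails when both conditions fail together, because the larger group then dominates the pooled variance.

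This design secures neither condition. Group size follows patient choice. Equal spread is open to doubt for some scores: after L-ISR bowel function may range from good to poor continence, whereas L-ELAPE leaves a permanent colostomy. Section 2.3.1 adds a further source of mixing within L-ISR: "Prophylactic ileostomy will be performed for selected patients with higher risk of anastomotic leakage in the L-ISR group".

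At stake are the p-values and confidence intervals of the primary score comparisons. They would be too optimistic if the smaller group is the more variable, and too cautious if the larger group is. Which of these applies cannot be known before patients have chosen.

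**Working it through.** **Inputs from the article.** 72 evaluable patients per group, 144 in total (section 2.5); allocation by patient choice (2.1); Student t test (2.7). The article has no figure of its own to reproduce on this point.

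**Inputs assumed.** A two-sided 5% level, the realised split, and the ratio of the SDs. The article gives none of these for the scores, so a range is shown.

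**Formulas.** With sizes n1, n2 and SDs s1, s2:

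- True variance of the mean difference: V = s1²/n1 + s2²/n2
- Variance that the Student test works with: P = [((n1−1)s1² + (n2−1)s2²)/(n1+n2−2)] × (1/n1 + 1/n2)
- Approximate type I error: 2 × [1 − Φ(c × √(P/V))], where c = 1.977 is the t critical value on 142 degrees of freedom

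**Planned split, 72/72, SDs 1.5 and 1.** V = (2.25 + 1)/72 = 0.0451. P = 1.625 × 2/72 = 0.0451. P/V = 1, so there is no distortion.

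**48/96, smaller group more variable (SD 1.5 against 1).**

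- V = 2.25/48 + 1/96 = 0.0573
- Pooled variance = (47 × 2.25 + 95 × 1)/142 = 1.414, so P = 1.414 × 0.03125 = 0.0442
- V/P = 1.30, so the standard error used is 0.878 of the true one
- c × 0.878 = 1.736, which gives about 8.3%

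**48/96, larger group more variable.**

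- V = 2.25/96 + 1/48 = 0.0443
- Pooled variance = (95 × 2.25 + 47 × 1)/142 = 1.836, so P = 0.0574
- The standard error used is 1.139 times the true one
- c × 1.139 = 2.25, which gives about 2.4%

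The approximation runs slightly low (it returns 4.8% where the true level is 5%). Simulation with 200,000 normal data sets per scenario and no true difference gives:

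| Split (N = 144) | SD ratio | Student, smaller group more variable | Student, larger group more variable | Welch |
|---|---|---|---|---|
| 72/72 | 1.5 | 5.0% | 5.0% | 5.0% |
| 58/86 | 1.5 | 6.9% | 3.5% | 5.0% |
| 48/96 | 1.5 | 8.4% | 2.6% | 5.0% |
| 48/96 | 2 | 11.0% | 1.7% | 5.0% |
| 36/108 | 1.5 | 10.6% | 1.8% | 5.0% |
| any of these splits | 1 | 5.0% | 5.0% | 5.0% |

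In the 72/72 row the two groups are the same size, so the two Student columns differ only by simulation error.

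**Sex-specific scores.** IPSS and IIEF-5 are for men and FSFI is for women, so these comparisons have fewer than 144 patients, and their split may differ from the overall one. The distortion depends mainly on the split and hardly on the total: at an assumed 24/48 with SD ratio 1.5, V/P is again 1.30.

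**The case against.** A reader might infer that the score spreads are expected to differ, and that the planned p-values and intervals are therefore wrong. The article does not support this. It reports no SD and makes no statement about relative spread, and the planned ratio is 1:1, at which the Student test keeps its level. Every unfavourable figure above needs an assumed split and an assumed SD ratio together. This part of the objection stands, and the point is worded accordingly.

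The reason to expect unequal spread is also limited in reach. The ileostomy is temporary, with closure planned 3 to 6 months after surgery in a 3-year follow-up, so it bears mainly on the early visits. Stoma status says little about the spread of the urinary, sexual or general quality-of-life scores. The argument is plausible for the Wexner and bowel-related scores and has no documented basis for the rest.

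Nor can the point be extended to a failed non-inferiority conclusion. The only planning rates in section 2.5 concern incomplete CRM, which is binary and not a matter for a t test, and the text gives no margin for any score.

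Finally, variance handling is often settled in an analysis plan, which is not shown here, and section 2.7 specifies that "SPSS for Windows, version 22.0 (IBM Corp, Armonk, NY) will be used for statistical analysis", a package that prints both versions of the test. That lowers the weight of the point without removing it. The article names a specific test, and if the version is not fixed in advance, the choice between two printed lines could be made after the results are seen.

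**Conclusion.** The point holds as a conditional risk of minor weight. The article names the Student test, and nothing in the design secures the equal group sizes that would protect it against unequal spread. If both inequalities occur, the nominal 5% becomes about 8.4% or 2.6% at an assumed 48/96 split and SD ratio of 1.5. Over the assumed scenarios at ratio 1.5 it ranges from about 7% to 11% in one direction and from about 3.5% to 1.8% in the other. The direction depends on which group is smaller and on which is more variable. With equal sizes or equal SDs the effect is nil. The figures rest on normal data and on assumed splits and SD ratios. The recommendation is an improvement that costs nothing; it does not correct an error that the documents prove. The reversed pairing of tests and data types in the same sentence is, by contrast, a plain wording error.

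**What to change.** Rewrite the sentence in section 2.7, for example: *Continuous outcomes will be compared between the two groups by the unequal-variance (Welch) t test, reported with its confidence interval, and categorical outcomes by the chi-square test.* Changing only the name of the t test would leave the reversed pairing in place. If a regression or mixed model is used for the scores, allow a separate residual variance per group or use robust standard errors.

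The cost is one sentence. SPSS already prints the unequal-variance line beside the pooled one. At 1:1 the two tests have the same standard error and differ only in degrees of freedom, so the loss of power is negligible.

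The change does nothing about confounding from patient choice, which affects any unadjusted comparison here and has to be dealt with separately.
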